### The intervention group

All included patients have been discharged from a psychiatric hospital at The Capital Region of Denmark during the period from May 2017 to October 2018 following an affective episode (depression or mania). All included patients continue standard treatment-as-usual at a community psychiatric centre, a private psychiatrist, a general practitioner or outpatient treatment at a hospital during the trial period.

#### The smartphones

In the RADMIS trials, the Monsenso system is available for smartphones capable of collecting subjective and automatically generated behavioral data on measures of illness activity. All patients randomized to the intervention group are offered the loan of an Android smartphone free of charge for the 6-month trial period. The patients in the intervention group are encouraged to use the Monsenso system for daily electronic self-monitoring. Economic costs from data traffic due to the RADMIS trials are refunded to all participants regardless the choice of smartphone type.

##### Subjective (self-monitored) measures of illness activity in the intervention group

The patients randomized to the intervention group, regardless the choice of smartphone are, on a daily basis, prompted by an alarm in the Monsenso system at a self-chosen time during the day to evaluate subjective measures of illness activity.

The following subjective (self-monitored) measures of illness activity are available for daily evaluation for patients with unipolar disorder as well as bipolar disorder: sleep duration (number of hours slept per night, measured in half-hour intervals), time of falling asleep the previous evening (hh:mm), time woken up the following morning (hh:mm), medicine intake (taken as prescribed/taken with changes (if changes, the patients are asked to specify these)/not taken), anxiety (scored from “not present,” “present to some degree” or “present” on a scale from 0, 1, 2), cognitive problems (scored from “not present,” “present to some degree” or “present” on a scale from 0, 1, 2), alcohol consumption (number of units consumed per day, 0 to +10 scale), stress (scored from “not present,” “present to some degree” or “present” on a scale from 0, 1, 2), menstruation for women (yes/no), individual early warning signs (yes/no), a number (unlimited) of personal parameters (created by the patients themselves), and a free-text note.

Suicidal thoughts will not be evaluated as part of the self-monitoring due to ethical concerns and since deterioration, leading to suicidal thoughts, will be reflected on other of the self-monitored parameters in the system. Suicidal patients will be treated using standard care and taken care of by the usual clinician.

In addition to these items, the following self-monitored measures of illness activity are available for daily evaluation *specifically* for patients with unipolar disorder: mood (scored from “euthymic” to “depressive” on a scale from 0, −0.5, −1, −2, −3), activity level (scored from “normal” to “very low” on a scale from 0, −1, −2, −3), irritability (scored from “not present,” “present to some degree” or “present” on a scale from 0, 1, 2). Similarly, the following additional self-monitored measures of illness activity are available for daily evaluation *specifically* for patients with bipolar disorder: mood (scored from “depressive” to “manic” on a scale from −3, −2, −1, −0.5, 0, +0.5, +1, +2, +3), activity level (scored from “very low” to “very high” on a scale from −3, −2, −1, 0, +1, +2, +3), mixed mood (yes/no), irritability (scored from “not present,” “present to some degree” or “present” on a scale from 0, 1, 2).

After midnight, the entered subjective (self-monitored) measures of illness activity are “locked” and further changes cannot be made. If the patients wish to change their subjective evaluation they can enter a second evaluation in addition to the initial one, and both of the subjective evaluations are then visible for the patient and the health care provider when logging on to in the Monsenso system. If the patients forget to evaluate the subjective measures it is possible to enter and evaluate retrospectively for up to 2 days. It is then noted in the Monsenso system that the subjective measures are collected retrospectively. Screenshots from the Monsenso system are presented in Figs. 3 and 4. A user’s guide for the Monsenso system was developed and handed out to all patients in the intervention group (can be obtained by contacting the corresponding author).

**Fig. 3 Fig3:**
[figure not shown]
The Monsenso self-assessment system. Screenshot of the smartphone-based self-assessment

**Fig. 4 Fig4:**
[figure not shown]
The Monsenso self-assessment system. Screenshot of the smartphone-based self-assessment of mood

##### Automatically generated behavioral data (objective data) on measures of illness activity

Smartphones are capable of collecting automatically generated behavioral data on measures of illness activity on a daily basis (objective data) during the 6-month trial period.

Examples of some of the automatically generated behavioral data on measures of illness activity collected by the smartphones: (1) phone usage measured as the number of times and amount of time the smartphones screen are turned on/off, battery usage, ambient light, and “proximity” detection, (2) social activity measured as the number of in- and outgoing phone calls and text messages, the duration of in- and outgoing phone calls, the length of the text messages, and the time of the day when the phone calls and/or text messages are made/sent/received, (3) physical activity measured by the step counter in the smartphones, and (4) mobility based on the location estimation available in the smartphones (which again rely on, e.g., GPD or GSM cell tower information depending on specific circumstances). Furthermore, speech activity is collected by extraction of different voice features during phone calls. Voice feature extraction will take place directly on the smartphones and no recording of the actual speech/conversation will take place. The intention is to synthesize these automatically generated behavioral data into one aggregated objective composite measure.

##### Smartphone-based CBT modules

The smartphone-based CBT modules include four modules: psychoeducation, behavioral activation, cognitive restructuring and rumination-focused CBT. The psychoeducation and mood-monitoring system include strategies for detecting and intervening with early signs of relapse. Patients are encouraged to use the module in an individualized and sequential way according to their condition, affective state, and insight and following guidance from the study nurse if wanted. The behavioral activation module was inspired by Martell et al. (2010) and Lejuez et al. (2001) [41, 42]. It includes activity monitoring and activity scheduling and focus on regulation of sleep and daily routines. Several studies have established the efficacy for behavioral activation for treating depression [43–46] including a few studies of behavioral activation using smartphones; however, not including a control standard treatment arm [47, 48]. Further, regulating patterns of activity and sleep are helpful in reducing both depressive and manic symptoms [43, 49].

The cognitive restructuring includes simple techniques to help patients to identify and modify dysfunctional automatic thoughts. Cognitive restructuring is a key element of CBT and is included in a number of studies that show the efficiency of CBT in the treatment of depression including some studies of Internet-based CBT [50, 51], and a few studies including patients with bipolar disorder [20, 22].

A main purpose of the smartphone-based CBT modules was to help patients to reduce depressive ruminations. Therefore, a specific rumination-focused CBT strategy, based on the theory and practice described by Watkins et al. [25], was included. Rumination-focused CBT has shown encouraging results in the treatment of residual depression [25] and the Monsenso system includes the identification and reduction of unhelpful ruminations.

##### The integrated feedback loop between patients and clinicians

Study nurses with experience with unipolar disorder and bipolar disorder are assigned to the patients allocated to the intervention group of the RADMIS trials. The RADMIS study nurses are responsible for the integrated feedback loop. Patients allocated to the intervention group of the RADMIS trials will have the Monsenso application installed on a smartphone. The smartphone automatically transfers the self-monitored subjective measures and, for some smartphones, also the automatically generated behavioral data on measures of illness activity to servers at the hospital through secure connections (I-suite number RHP-2011-03). By giving informed consent to participate in the RADMIS, the patients allow for the RADMIS study nurses and their health care provider to access the monitored data through a secure web interface. The RADMIS study nurses go through the collected data approximately two to three times a week, or more often on patients where it is deemed necessary. A personal homepage is set up on a server allowing the patients to access all their own data through a similar secure web interface.The feedback loop on subjective measures: regardless the type of smartphone a feedback loop on the subjective measures is established. A standard of scoring thresholds for when the RADMIS study nurses initially should react was made. For example, the RADMIS study nurses react if the patients register ≥ −2 on the mood item for 2 days or more, or if the patients register changes in their sleep patterns of 1 h or more for more than 3 days. Following a run-in phase of approximately 2 to 4 weeks of self-monitoring, the patients and the RADMIS study nurses individualize the thresholds for when reaction should be made. Also the RADMIS study nurses and the patients agree on a concordance status in (a) the patients’ most important items for identifying prodromal symptoms of depression as well as (hypo)mania (only for patients with a bipolar disorder diagnosis), (b) the threshold for future early warning signs, and (c) actions to be taken in case of depression or (hypo)mania (only for patients with a bipolar disorder diagnosis)The integrated feedback loop on subjective and automatically generated behavioral data on measures of illness activity: a feedback loop integrating subjective and automatically generated behavioral data on measures of illness activity is established. The feedback loop integrates both subjective and automatically generated behavioral data on measures of illness activity in a flexible and adjustable model (a learning system) resulting in prediction analyses of the collected data providing messages for both the patients and the RADMIS study nurses such as: “You are invited to contact your RADMIS study nurse.”

Actions taken by the RADMIS study nurses, as part of the feedback loop in the intervention group, in case of signs of deterioration of a patient in the intervention group:Contact the patient and give advice on how to handle the situationIf the first action is not enough, the study nurses ask the patient to contact the usual physician or other clinicianIf the above actions are not enough, or if contact with the patient is not possible, the study nurses contact the patient’s usual physician or other clinician themselvesIn case of acute deterioration and/or severe symptoms, the study nurses recommend the patient to contact the psychiatric emergency service in Copenhagen, Denmark

The Monsenso system was designed in an interactive process between patients with unipolar disorder, bipolar disorder, IT researchers, clinicians, and clinical researchers before the beginning of the RADMIS trial.

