Although psychiatric treatment internationally, and in Denmark, has shifted more from inpatient treatment to outpatient treatment during recent decades, costs due to psychiatric hospitalization are still a major burden comprising two thirds of all direct costs in the five Regions of Denmark [5]. Patients with affective disorders are more frequently hospitalized than any other patient group, counting more than 10,800 patients in 2013 among the entire Danish population of 5.4 million people, and 20% of all psychiatric hospitalizations in Denmark [6]. The cost of these hospitalizations alone is estimated to be DKK648 million (approximately €8.7 million) per year in Denmark (10,800 hospitalizations with a mean of 20 days’ stay for a cost of 3000 DKK/day (€400)). The discharge period after hospitalization is a high-risk period with a more than 300 times increased risk of suicide during the first week [7] and a high risk of re-admission [8, 9]. Patients are often afraid of leaving the hospital, feeling alone with the prospect of an appointment with a physician 1 or more months ahead. A pilot study from our group in which 45 patients discharged from psychiatric hospital self-monitored symptoms using a daily computer-based self-monitoring system emphasized the pivotal importance of continued contact with a clinician such as a nurse [10]. Smartphones comprise a unique platform for the monitoring and treatment of depression and mania. Depression and mania are associated with changes in several behavioral components (e.g., reduction in activity level, change in speech) and motivational states (e.g., anhedonia), some of which may be detectable using readily available smartphone sensors [11–13]. Prior work done by our group has developed and tested a unique smartphone-based system for the treatment of bipolar disorder (the MONARCA system) [14, 15]. The MONARCA system is capable of collecting subjective self-assessment data and automatically generated objective smartphone data from patients on a daily basis while allowing simple bidirectional communication between clinicians and the patients [15]. We find it likely that daily contact with a psychiatric hospital nurse using a bidirectional feedback system combined with objective smartphone-based early warning signs, assessed using a smartphone app, will reduce the risk of re-admission and the risk of relapse of depressive and (hypo)manic symptoms.

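### The example mood threshold for a nurse reaction (≥ −2) contradicts the direction of the protocol's own mood scales

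*Protocol article*

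**What the plan says.** The protocol article's section on self-monitored measures defines the mood item separately for each diagnosis. For unipolar disorder the item is "mood (scored from “euthymic” to “depressive” on a scale from 0, −0.5, −1, −2, −3". For bipolar disorder it runs from depressive to manic "on a scale from −3, −2, −1, −0.5, 0, +0.5, +1, +2, +3". In both, a more negative score means a more depressed mood.

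The section on the integrated feedback loop then describes when nurses respond. It states: "A standard of scoring thresholds for when the RADMIS study nurses initially should react was made". Two examples follow. The first concerns mood: nurses "react if the patients register ≥ −2 on the mood item for 2 days or more". The second is an alternative trigger based on a sleep change of at least 1 h lasting longer than 3 days. The standard is later replaced: "Following a run-in phase of approximately 2 to 4 weeks of self-monitoring", patient and nurse agree individual thresholds. The same section lists the steps nurses take and ties them to signs that a patient is getting worse.

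**The concern.** The inequality points the wrong way for a scale on which worse depression is more negative. Taken as printed, a euthymic patient scoring 0 on two days meets the threshold, while a patient scoring −3 on two days does not. The two sections therefore contradict each other, and the rule also conflicts with the purpose given for the nurse actions.

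The feedback loop is a named part of the intervention under test, and this is the only mood threshold the article prints. Someone wishing to understand or repeat this part of the intervention has to override the text to make sense of it. For bipolar patients, overriding it still does not yield a single rule. The standard also covers the weeks just after discharge, a period for which the Background section cites a "more than 300 times increased risk of suicide during the first week". That is a reason to have the sentence right. It is not evidence of an effect on patients.

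**Working it through.** No sample size, power or error rate is involved, so there is no figure of the plan to reproduce. The check applies the printed rule to every value on each scale.

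**Inputs**
- Rule: score ≥ −2 for 2 days or more (section on the integrated feedback loop).
- Unipolar scale, 5 levels: 0, −0.5, −1, −2, −3 (section on self-monitored measures).
- Bipolar scale, 9 levels: −3, −2, −1, −0.5, 0, +0.5, +1, +2, +3 (same section).

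**Step 1: the rule as printed.**
- Unipolar: 0, −0.5, −1 and −2 meet it (4 of 5). Only −3 does not.
- Bipolar: −2, −1, −0.5, 0, +0.5, +1, +2 and +3 meet it (8 of 9). Only −3 does not.

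**Step 2: severity readings, listed only to show how far apart the interpretations lie.**

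| Reading | Unipolar levels meeting it | Bipolar levels meeting it |
|---|---|---|
| As printed, score ≥ −2 | 0, −0.5, −1, −2 (4 of 5) | all except −3 (8 of 9) |
| Severity, depressive side only | −2, −3 (2 of 5) | −3, −2 (2 of 9) |
| Severity, distance from 0 of at least 2 | −2, −3 (2 of 5) | −3, −2, +2, +3 (4 of 9) |

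**Step 3: disagreement between readings.**
- Unipolar: the two severity readings coincide. Each differs from the printed rule at 0, −0.5, −1 and −3, which is 4 of 5 levels. They agree only at −2.
- Bipolar: the two severity readings differ from each other at +2 and +3. The article does not choose between them. It does say that the individual agreements made after the run-in cover (hypo)mania in bipolar patients, so the manic side matters to the loop, but the example threshold is silent on it.

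**Step 4: duration.** The initial standard holds for about 2 to 4 weeks of a 6-month period. Taking 6 months as about 26 weeks, that is 2/26 ≈ 8% to 4/26 ≈ 15% of follow-up, in an intervention arm of 100 planned patients per trial.

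These are counts of scale levels. They do not say how many patients would be contacted or missed, because the article gives no distribution of daily mood scores.

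**The case against.** The strongest reply is that the meaning is plain. The unipolar scale is printed in order of increasing severity, the nurses are experienced in these disorders, and they are told to act on deterioration, so the sign most naturally means at least as severe as −2. The rule is introduced as an example from a standard that the article does not reproduce in full, as a condensed article may, and individual thresholds soon replace it.

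Much of this stands. The likely intent is a severity reading, and the absence of the full standard is no fault. What does not stand is that the sentence can be left alone. A rule that is printed is not a detail left to another document. Nothing in the text says that the sign refers to severity, and the severity reading does not settle the bipolar case.

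A reader might go further and infer that the feedback loop cannot work, that this trigger is the only safety response to worsening mood, that patients would be harmed, or that an automatic alert was set wrongly. The article does not support any of these:
- Nurses review the data about two to three times a week, and more often where they judge it necessary.
- A sleep trigger stands beside the mood trigger as an alternative.
- A separate integrated loop produces predictions and messages.
- The escalation steps for deterioration are not tied to the mood threshold.
- All patients continue usual treatment, and suicidal patients are left to standard care.
- No automatic alert on the mood item is described. The loop on subjective measures is described as nurses going through data and reacting.

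**Conclusion.** The contradiction holds. The example threshold, read on the article's own scales, is met at euthymic mood (4 of 5 unipolar and 8 of 9 bipolar levels) and not met at the most depressed level. This rests only on the printed inequality and the printed scales.

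Its reach is narrow. It affects how one part of the intervention is described and whether that part can be repeated from the text. The primary outcome comes from a national register, and no endpoint definition, sample size, error rate or analysis uses the rule. Nothing shows that nurses applied it literally. It still deserves correction, because it is a stated decision rule in the tested intervention that selects the wrong scale levels for its purpose if followed, and because its coverage of the manic side is undetermined.

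**What to change.** Reconcile the section on the integrated feedback loop with the section on self-monitored measures. For each diagnosis, list the mood-scale values that lead to a nurse reaction under the initial standard. For bipolar disorder, state explicitly whether positive values are included. Naming the scale values avoids any doubt about the direction of an inequality on a negative scale. Then confirm that the nurse instructions carry the same rule, and report which rule was in use. Which values should trigger a reaction is for the investigators to state, and none is proposed here.

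The cost is one sentence in the protocol and a check of the nurse instructions. No analysis changes.

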### The control group

Patients allocated to the control group continue with their standard treatment-as-usual and are asked to continue communicating as usual using their mobile phone (smartphone).

### Assessments

Researchers blinded to the patients’ allocation of intervention group ([name] and one other physician) who are not involved in the treatment of the patients carry out all outcome assessments. The unipolar disorder or bipolar disorder diagnoses according to ICD-10 are confirmed by a SCAN interview before inclusion of the patients. The patients are, regardless of randomization group, enrolled for a 6-month trial period and invited for outcome assessments by researchers blinded to intervention at baseline, after 3 months and after 6 months (Table 1).

At each visit with the researchers, the assessments include the following:

1. Clinician-administrated rating scales: the severity of depressive and manic symptoms (manic symptoms only assessed for patients with a bipolar disorder diagnosis) is measured using the Hamilton Depression Rating Scale 17-item (HDRS-17) [52] and the Young Mania Rating Scale (YMRS) [34], respectively, and psychosocial functioning is measured using the Functioning Assessment Short Test (FAST) [53]

2. Questionnaires: perceived stress according to Cohen’s Perceived Stress Scale [54], quality of life according to the WHO Quality of Life-BREF (WHOQOL-BREF) [55], self-rated depressive symptoms according to Beck’s Depressive Inventory (BDI) [56–58], self-rated depressive symptoms according to the Hamilton Depression Self-rating Scale 6-item (HDRS-6) [59], self-rated manic symptoms according to Altman Self-rating Scale for Mania (ASRM) (only for patients with a bipolar disorder diagnosis) [34], recovery according to the Recovery Assessment Scale [60], empowerment according to Rogers’ Empowerment Scale [61], adherence to medication according to the Medicine Adherence Rating Scale [62], wellbeing according to the WHO (five) Wellbeing Index [63], rumination according to the Ruminative Response Scale (RRS), worrying according to the Penn State Worry Questionnaire (PSWQ) [64], and satisfaction according to the Verona Satisfaction Scale-Affective Disorder (VSS-A) [65]. The patients are asked to fill out HDRS-6, ASRM (only for patients with a bipolar diagnosis) and WHO (five) every month during the 6-month trial period in both groups and in both trials.

